### Summary

Green tea from the leaves of *Camellia Sinensis* is one of the oldest and most popular beverages worldwide. Green tea extract contains around 30-70% polyphenols of which (-)-Epigallocatechin-3-gallat (EGCG) is the most important compound. This major compound of green tea (approximately 50% of total catechins) shows positive effects on the cardiovascular system but also a preventive effect on tumor growth during cancer development. Green tea extract capsules normalized to a definite amount of EGCG are available on the market as dietary supplements, but green tea extract is also added to other food products and beverages. In this study we want to study the influence of genetic variants in genes of the biotransformation and drug transport on the kinetics of EGCG and other green tea catechins after one week of daily oral intake of green tea extract capsules with 300mg EGCG on healthy volunteers. Plasma-concentration-time profiles of n=100 healthy participants will be studied after 4 day twice daily (morning and evening) intake of 2x150mg (=300mg EGCG) with 12h gap in-between. On day 5 the blood concentrations of EGCG will be measured for 10h after the controlled intake of one capsule with 150mg EGCG. The oral EGCG clearance as well as nutrikinetic data of further catechins (measured as Dosage/AUC) after intake of 150mg EGCG under fasting conditions should be analyzed in relation to pharmacogenetics variants in transporter genes (e.g. OATP1A2 and OATP1B3) and in genes of the biotransformation of EGCG for example Catecholamin-O-Methyltransferase (COMT), Glutathiontransferase and Sulfotransferase.

This study should allow a better understanding of individual variability in the kinetic of EGCG, which has an influence on the individual efficacy of green tea intake.

## Participants

N=100

**Study Design:** open, Nutrikinetic study

**Planned number of participants** 100

**Study duration for each participant** Intake of two times 150mg EGCG over 4 days, followed by blood sampling over 1d (10h)

**Study duration:** 18 month

## 2. Introduction

### 2.1 Transport and Biotransformation of EGCG

Green tea catechins are resorbed in the small intestine as monomer Flavan-3-ole. Catechins reach their maximal plasma concentration after 1-4 hours and to more than 99% they are excreted 24h with plasma half live of 3h. [1, 2]. EGCG is actively transported in hepatocytes and intestinal epithelium cells over the transporter OATP1A2 and 1B3 [3]. Additionally EGCG is transported over an efflux transport with MRP-1 and MRP-2 into the intestinal lumen or from liver cells. P-glycoprotein (MDR1) is inhibited by green tea catechins (EGCG and others) but is not transporting catechins [4]. In the liver catechins are mainly metabolized by phase II enzymes (glucuronidated, methylated and sulfated). Methylation was described over the genetic polymorph enzyme Catechol-O-Methyltransferase (COMT) and COMT is also inhibited by EGCG [5]. EGCG is mainly eliminated biliary within the first 6h after intake.

### 2.2 Nutrikinetics of EGCG

EGCG is quickly absorbed after oral administration (capsule) and reaches the maximal blood concentrations after 1-2 hours. After single dose administration of 400mg EGCG capsules maximal plasma concentration of 112ng/ml and an AUC of 623ng/ml\*h was measured, after a single dose of 800 mg EGCG 438ng/ml and an AUC of 2779 ng/ml\*h was determined [6]. The half-life time of EGCG in plasma is 2-4 h. The intake of 400 mg and 800 mg over 4 weeks does not lead to any accumulation (under multiple dosing values measured 24 h after the last administration were below limit of detection), because the half-life time is too short (see figure1). Nevertheless AUC of a 800 mg doses was 60% under multiple dosing than single dosing. This might be due to an inhibition of presystemic intestinal metabolism. Splitting 800mg/day into several single doses leads therefore to higher blood levels than a single dose [7-9]. EGCG can be found mostly unbound in the plasma (92%), is biliary eliminated and can be neither detected in its conjugated nor glucuronidated form in urine [7-9]. In figure 3 the time-plasma concentration profiles after administration of 800mg and 400mg EGCG capsules are presented. Dots represent the profile after single dose (“before”), triangles represent the profile after 4 weeks of intake (“after”).

[figure not shown]

**Fig. 1:** Plasma concentration profiles after administration of 800mg and 400mg EGCG capsules after single doses (dots) and 4 week soft intake (triangles) Fig. from ref. [7].

### 2.3 Genetic polymorphisms in COMT, OATP1A2 and 1B3

Intestinal and hepatic influx transporter, as well as the (mainly hepatic) efflux transporter of EGCG and transporter and enzymes involved in biotransformation show genetic variability. Catecholamin-O-transferase (COMT) is an enzyme expressed in liver, kidney and brain and is involved in the methylation of neurotransmitters and xenobiotics. EGCG is methylated via COMT. This could in principle explain the interesting effect on the catecholamine metabolism (most probably outside the brain). A genetic polymorphism is described resulting in an amino acid exchange from valine to methionine. This change results in a trimodal distribution of enzyme activity with high activity in carriers with Val/Val form, medium activity in carriers with Val/Met and low activity in carriers of the Met/Met genotype. [10].

Many genetic variants are described in OATP1A2 and 1B3 transporter, but is not yet studied to which extent these variants effect the transport of EGCG.

## 3. Aim of the Study

In this study we will investigate the pharmacokinetic after multiple oral dosing of 300mg EGCG daily after 4-days of intake in relation to pharmacogenetics variants. It is the aim to compare the oral clearance (Dosage/AUC) as well as further pharmacokinetic parameters of EGCG as Cmax, Tmax, T1/2 in carriers of different genotype variants.

## **4. Study population**

### **4.1. Informed consent and regulation**

Essential requirement for the participation of a test person in this trial is a written consent after he was written and orally informed about the study. This study is conducted in agreement with the Declaration of Helsinki (in revision from Edinburgh, October 2000), the principle of Good Clinical Practice (GCP), of the International Conference of Harmonization (ICH) and other national regulations and guidelines. The participants are informed on all aspects of the study in an information leaflet. The information of the participant is documented by the clinical study investigator together with the written consent of the participant.

### **4.2. Inclusion criteria**

- Healthy male and female participants after physical check up
- German or northern European origin (to obtain a genetic homogenous population, no intention to racism)
- Written informed consent
- Age > 18 years
- BMI between 18 and 30

### **4.3. Exclusion criteria**

- For female pregnancy and breast feeding
- Acute and chronic disease
- Each acute infectious disease (start of the participation can be delayed)
- Regular drug intake with exception to oral contraceptives
- Need to take drugs during study period and especially at study day (e.g. analgesics or antibiotics).

### **4.4. Stop criteria for each participants**

- Withdrawal of consent.
- Occurrence of an occasion or an adverse event which in opinion to the clinical study investigator makes it useless to continue the study

### **4.5. Stop criteria for the study**

Stop criteria for the study are not defined. The occurrence of severe adverse events which relative unlikely due to millions using green and black tea every day, but it cannot be completely excluded for the extract capsules used in this trial. Certainly, we will discuss the stopping of the study whenever a severe adverse event happens which is in clear causality with the test drug.

### **4.6. Number of participants**

100 participants, which completed the protocol and can be analyzed.

## **5. Duration of the study**

### **5.1. Start and duration of the study**

The start of the study is planned for September 2011. Each participant spends one day on the research ward. For 100 participants around 18 months are planned.

### **5.2. Duration for each participant**

The study duration for each participant is four days intake of capsules at home plus one day on the research ward (study day).

## **6. Execution of the study**

### **6.1. Preliminary check-up**

Interested persons will be written and orally informed about the aim, procedure, risks and duration of the study. After written consent a blood sample for genotyping is taken. For this reason 9 ml of venous EDTA blood is taken. If the participant is a carrier of a wanted genotype an appointment for a preliminary check-up is arranged. At this preliminary check-up a physical check-up is made and laboratory parameters are analyzed from blood giving information on the health status of the participants. Following parameters will be determined: Blood cell count, creatinine, bilirubin, GOT, GPT,  $\gamma$ GT and a pregnancy test for women. According to the results a decision on inclusion in the study is made.

### **6.2. Study drug**

A commercially available green tea extract with an EGCG content of 50% is used. Green tea extract, cellulose and MG-stearate is capsuled in gelatin capsules. The capsules are produced by [name], Hamburg. The green tea capsules are identical to the ones used in a multicenter trial to study the effect of green tea extract on the development of colon adenomas (see also ethics approval 68/09).

One capsule contains 150mg EGCG and around 300mg total catechins

Great importance is attached to the fact that the complete medication is from a single batch. The substance is stored under dry (<60% humidity) and light-protected conditions at a room temperature of 25°C.

The drug intake at study day is supervised and documented with the exact time point. Drug should be taken with 200ml tap water without carbon dioxide.

### **6.3. Study Procedure**

Day 1-4:

Participants get for four day in the morning and with a gap of 12h in the evening one capsule with 150mg EGCG respectively 300mg EGCG per day. They are asked to take the capsule with breakfast or dinner with one glass of tap water.

Study day:

At study day, participants appear in the morning under fasting conditions at the research ward. After a short physical check-up, a venous line is established and a blood sample for the basal level of kinetics is taken. The participants take one capsule with 150mg EGCG with one glass of tap water. In the following ten hours blood samples for the analysis of the EGCG plasma concentration is taken. After 4h and 10 h participant get a meal and a snack. No other food is allowed during their stay on the research ward.

**6.4 Schema:**

| Day  | 0.00                                                             | 0:30          | 1.00                                                                                                                          | 2:00                                                  | 3:00                  | 4:00                            | 5:00                  |  | 7:00                  | 9:00                      | 20:00                  |
|------|------------------------------------------------------------------|---------------|-------------------------------------------------------------------------------------------------------------------------------|-------------------------------------------------------|-----------------------|---------------------------------|-----------------------|--|-----------------------|---------------------------|------------------------|
| -x   | Preliminary check-up, blood sample: RNA, DNA, EDTA-Plasma |               |                                                                                                                               |                                                       |                       |                                 |                       |  |                       |                           |                        |
| -4   | 1Cps.
150mg
EGCG                                           | à             | ← →
Intake at home, participants have to document the intake and adverse event in a diary in order to increase compliance. |                                                       |                       |                                 |                       |  |                       |                           | 1Cps.
150mg
EGCG |
| -3   | 1Cps.
150mg
EGCG                                           | à             |                                                                                                                               |                                                       |                       |                                 |                       |  |                       |                           | 1Cps.
150mg
EGCG |
| -2   | 1Cps.
150mg
EGCG                                           | à             |                                                                                                                               |                                                       |                       |                                 |                       |  |                       |                           | 1Cps.
150mg
EGCG |
| -1   | 1Cps.
150mg
EGCG                                           | à             |                                                                                                                               |                                                       |                       |                                 |                       |  |                       |                           | 1Cps.
150mg
EGCG |
| 1    | BE-0
(Predose): 1
Cps. 150mg
EGCG                       | BE-1:
10ml | BE-2:
10ml,
UAW                                                                                                         | BE-3:
40ml
BE:
RNA
DNA,
Plasma,
CRP | BE-4:
10ml,
UAW | BE-5:
10ml,
UAW,
Lunch | BE-6:
10ml,
UAW |  | BE-7:
10ml,
UAW | BE-8:
10ml,
UAW     |                        |
| Food | Fasten from
22:00 day -1                                      | **            | **                                                                                                                            | Small
snack
after
BE-3                       |                       | Lunch
after
BE-6          |                       |  | Snack                 | (Dinner
after
BE-9) |                        |
|      |                                                                  |               |                                                                                                                               |                                                       |                       |                                 |                       |  |                       |                           |                        |

BE: Blood sample for kinetic measurement; UAW: Adverse events; gray: Time on test station, HF: Heart rate; RR: blood pressure

\*\* If the participants suffers from hypoglycemia, 10g of glucose or a EGCG-free soft drink is allowed (better no juice)

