#### **6.7. Allowance and follow-up**

Follow-up includes a check-up similar to the Preliminary check-up and performed after the study day. Participants get an allowance of 80€.

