## **7.3 Secondary outcome**

Maxima blood concentration (Cmax), Time of the maximal blood concentration (Tmax), half life time (T1/2), adverse events, changes in gene expression profiles, epigenetic changes in blood cells, concentration profile of the used capsules including description of rate and variability of absorption, distribution (alpha half-life) and terminal elimination (beta half-life) of the relevant green tea catechins as far as they are detectable.

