### **8.6 Eating and drinking during study.**

One day before the study day participants should not drink tea, especially green tea. A list containing information about food which could contain EGCG or similar compounds is given to the participants ahead of study.

Participants must not eat from 22:00 the day before the study day until two hours after the intake of the study drug at study day. Afterward the participants get a bread roll, lunch and dinner during their stay on the research ward at study day. For the choice of the dish, attention will be payed that the food does not contain EGCG or similar substances. For drink participants get mineral water.

Because it is known that nutrikinetic of EGCG is influenced by food intake (more than 3-times higher blood levels under fastened then fed conditions) participants should not eat additional food. No more than 3L of water is allowed to be drunk during study day

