## **9. Adverse Events**

### **9.1 Definitions**

An **adverse event (AE)** is any untoward medical occurrence in clinical investigation subject and which does not necessarily have a causal relationship with this treatment.

It includes every untoward medical occurrence in a patient or clinical investigation subject administered a pharmaceutical product or in our case a food supplement between first intake and 24hours after the last administration.

An adverse event (AE) can therefore be any unfavorable and unintended sign (including an abnormal laboratory finding), symptom, or disease temporally associated with the use of a medicinal (investigational) product, whether or not related to the medicinal (investigational) product

Preexisting Diseases which worsen during the study are also defined as AE. AEs can become serious adverse events if they fulfill following criteria.

A **serious adverse event (SAE)** is defined as each adverse event or side effect that independently from causality occurs between first administration and 24hours after the last administration and fulfills following criteria:

- results in death (remark: death is the consequence and not the event)
- is life-threatening, (remark: the term “life- threatening” describes an situation in which a patient is in danger to life, and not an event which could lead to death if it would have been more serious)
- requires inpatient hospitalization or prolongation of existing hospitalization,
- results in persistent or significant disability/incapacity, or
- is a congenital anomaly/birth defect.
- Event which leads to an action to prevent one of the above mentioned criteria.

An **adverse drug reaction** is defined as any adverse event (as defined above) for which a causality with the study is possible, likely or certain.

A **serious adverse drug reaction** is defined as any severe adverse event (as defined above) for which a causality with the study is possible, likely or certain.

An **unexpected serious adverse drug reaction** is a severe adverse event that is not a typical adverse event for the test drug or intervention documented in the information sheet for trial participants.

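### Adverse events count until 24 h after the last capsule, but no adverse-event recording is scheduled for the last 14–15 h of that window

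*Protocol*

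**What the plan says.** **The window.** Protocol 9.1 defines an AE as an untoward occurrence in someone given, "in our case a food supplement between first intake and 24hours after the last administration". The definition of a serious AE uses the same limits: it "occurs between first administration and 24hours after the last administration and fulfills following criteria". Section 7.3 lists AEs among the secondary outcomes ("adverse events, changes in gene expression profiles").

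**The recording.** The schema in 6.4 shows two means of recording:
- On the home days (rows -4 to -1): "Intake at home, participants have to document the intake and adverse event in a diary in order to increase compliance".
- On the study day (row 1): entries marked UAW, which the legend explains ("UAW: Adverse events; gray: Time on test station"). They stand at 1, 3, 4, 5, 7 and 9 h. The 20:00 cell of that row is empty, and the row has no diary entry.

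Sections 6.3 and 6.5 put the end of ward sampling at 10 h.

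**Afterwards.** Section 6.7 says: "Follow-up includes a check-up similar to the Preliminary check-up and performed after the study day". Section 6.1 describes the preliminary check-up as a physical examination and laboratory tests. Neither section mentions a question about AEs, and 6.7 does not say how long after the study day the check-up takes place.

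**The dose before the gap.** By 6.3 the home capsules are taken with breakfast or dinner and the study-day capsule is taken fasted. Section 8.6 gives the effect of fasting as "more than 3-times higher blood levels under fastened then fed conditions".

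**The concern.** The period over which events count is longer than the period in which the plan arranges to record them. A headache or stomach upset that starts on the evening or night after the study-day capsule is an AE by 9.1. It falls after the last ward check and outside the diary. It reaches the case report form only if the participant brings it up later without being asked.

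This is more than a detail that an analysis plan could settle, because no analysis can recover events that were never collected. It also affects the hours after the capsule that, by the protocol's own statement on food, gives the highest blood levels of the nine taken. At stake is the completeness of a stated secondary safety outcome. The primary outcome (oral clearance), the kinetic sampling and the sample size are not touched.

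**Working it through.** The protocol gives no AE rate and no figure for AE coverage, so there is nothing of its own to reproduce. The check compares the window with the schedule and then bounds what might be missed.

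**Step 1: length of the gap**

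Inputs: window end 24 h after the last capsule (9.1); last ward AE check 9 h (6.4); end of ward sampling 10 h (6.3, 6.5).

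- By the schema: 24 − 9 = 15 h.
- By the text: 24 − 10 = 14 h.

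The window runs from the first home capsule to 24 h after the study-day capsule: 4 × 24 + 24 = 120 h. The gap is therefore 14/120 to 15/120 = 11.7–12.5% of the window's hours, and 14/24 to 15/24 = 58–63% of the hours after the last capsule. These are shares of time, not of events.

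**Step 2: what the gap could hold if onset follows plasma concentration**

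Inputs: half-life 2–4 h (2.2). Assumptions not in the protocol: one-compartment oral kinetics, an absorption rate ka of 0.8–3 per h, onset risk proportional to concentration, and no capture at follow-up.

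With ke = ln 2 / half-life, the share of a single dose's area under the curve that lies after time T is

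(ka·e^(−ke·T) − ke·e^(−ka·T)) / (ka − ke).

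Example: half-life 4 h, ka 0.8, T = 9 h. Here ke = 0.1733 and e^(−ke·9) = 0.2102, and the second term is negligible, so the share is 0.8 × 0.2102 / 0.6267 = 0.268.

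| Half-life | Share after 9 h | Share after 10 h |
|---|---|---|
| 2 h | 5–8% | 4–5% |
| 3 h | 14–18% | 11–14% |
| 4 h | 22–27% | 19–23% |

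So 4–27% of the study-day risk would fall after the last scheduled check.

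**Step 3: the same on the scale of the whole window**

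Eight home capsules are taken with food (4 days × 2). By 8.6 fasted levels are more than three times fed levels, so give each home capsule one third of the fasted exposure. Total exposure in fasted-capsule units is 8 × 1/3 + 1 = 3.67.

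- Lowest: half-life 2 h, ka 3, after 10 h: 0.035 / 3.67 = 1.0%.
- Highest: half-life 4 h, ka 0.8, after 9 h: 0.268 / 3.67 = 7.3%.

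These shares include the small tail beyond 24 h. Cutting exposure off at 24 h lowers the upper end from 7.3% to 6.8%. The range remains about 1–7%. A food ratio above three would raise it somewhat, and any recall at follow-up would lower it.

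**The case against.** **The hours are not shown to be unobserved.** Every participant has a check-up after the study day (6.7). The protocol does not say that AEs are not asked about there; it is silent. Late symptoms could be recalled at that visit, and persisting changes in liver values would show in its laboratory tests. Section 9.3 requires AEs to be followed until they resolve or stabilise, and 10.1 lists AE documentation among the study documents. Instructions for the hours after discharge could also stand in the participant information, which is not available here. This stands as far as it goes: recording is not scheduled, which is weaker than saying that nothing can be seen. It does not close the gap. Section 9.3 deals with events already known, and a visit of unstated date with no stated question does not assure capture of a brief symptom during one night.

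**The 9 h figure comes from an imperfect table.** The schema refers to a tenth sample (BE-9) that has no column, and its shading for time on the ward is not visible in the copy reviewed. That is why 10 h is carried throughout as the alternative. The gap is 14 h even then.

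**A reader might infer a 12% understatement of AEs overall, or 58–63% for the study day.** The documents do not support this. It would need a constant onset rate, complete diary capture and no capture at follow-up, and the protocol gives no AE rates at all.

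**A reader might infer that a comparison of fasted and fed days is biased in favour of the fasted capsule.** No such comparison is planned in 7.2, 7.3 or 7.5. The direction is not clear either: six scheduled ward checks and continuous monitoring (8.7) may pick up more per hour than a self-completed diary.

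**Conclusion.** The mismatch stands on the text. Section 9.1 counts events to 24 h after the last capsule, while 6.4 schedules AE recording only in the home diary and in ward checks up to 9 h. The last 14–15 h, after the only fasted capsule, have no scheduled recording, and the later check-up in 6.7 has neither a stated time nor a stated AE question.

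The AE outcome is therefore liable to be under-recorded; it is not shown to be. The size cannot be derived from the protocol. If onset follows plasma concentration, about 1–7% of the whole-window risk lies in the gap, which may be small. That range rests on one-compartment kinetics with an assumed ka of 0.8–3 per h, the protocol's half-life of 2–4 h, a threefold food effect and no recall at follow-up. A correction is worth making because it is cheap and the data cannot be recovered later.

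**What to change.** - **6.4:** extend the existing diary to the study day, up to 24 h after the study-day capsule.
- **6.7:** state that the follow-up check-up takes place no earlier than 24 h after that capsule, that the diary is collected there, and that a standard AE question is asked.
- **6.4 and 6.5:** reconcile the 9 h and 10 h end points, so that the end of ward observation is fixed.
- **If the diary is not extended:** report study-day AEs for the observed 0–10 h only, and do not present them as covering the window in 9.1.

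The cost is one diary page, one question at a visit already planned, and a few more minor events to document. No extra visit, staff or participants are needed.
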